### Sample size

A previous study for *Guhong* injection in the treatment of angina pectoris [12] showed that the effective rate of the conventional treatment group (33 cases) was 81.82%, while that of the *Guhong* injection plus conventional treatment group (33 cases) was 93.94%. According to the literature, it was assumed that the efficiency rate of the *Guhong* injection group was from 81.82–93.94%, and the sample size was calculated based on the parameter *α* = 0.05 (bilateral test) and *β* = 0.2. By comparing the effectiveness rate of the two groups according to the following sample-size estimation formula:
$$ \mathrm{N}=\left[{\uppi}_{\mathrm{t}}\ \left(1-{\uppi}_{\mathrm{t}}\right)/\mathrm{k}+{\uppi}_{\mathrm{c}}\ \left(1-{\uppi}_{\mathrm{c}}\right)\right]\left(\ {\upmu}_{1-\upalpha /2}+{\upmu}_{1-\upbeta}\right)2/\left({\uppi}_{\mathrm{t}}-{\uppi}_{\mathrm{c}}\right), $$

we calculated that 111 patients should be recruited for each group. Taking into consideration an attrition rate of < 15%, the eligible participants in each group should be > 130. Ultimately, we determined the final sample size to be 130 (*N* = 260 in total).

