### Interventions

On the basis of conventional western medicine treatment, the *Guhong* group will be given a 20-ml intravenous infusion of *Guhong* injection that was diluted with 250 ml 0.9% sodium chloride injection once a day, while the control group will be given 270 ml 0.9% sodium chloride injection as placebo treatment once a day. (*Guhong* injection is provided by China tonghua guhong pharmaceutical co. Ltd. The production batch number is 20190306 and each bottle has a capacity of 5 ml. The drug distributed to each center will be labeled with the statement “for trial only” and the information of the name, dosage, dosing plan, indications, storage conditions, expiratory date, manufacturer and so on. Each center has an independent manager responsible for receiving, handling, storing and distributing the medications.) The course of treatment is 10 days. On the day of enrollment and at the end of treatment, the clinical symptoms and signs of angina pectoris will be recorded, the quantitative table of TCM syndrome will be scored, the electrocardiogram (ECG) will be examined, and the indicators of inflammation, endothelial function, myocardial metabolites and related biochemical tests will be conducted. Moreover, patients will be followed up for 8 weeks after the end of treatment, including any improvement in angina pectoris and the TCM syndrome quantitative score. During the entire study period, participants will be visited for a total of four times by the investigators. Specific research process details are provided in Table 2.

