#### Secondary outcomes

Secondary outcomes include changes in TCM symptoms and signs scores (Table 4), the average frequency of angina pectoris, the ECG, the indicators of inflammation, endothelial function and myocardial metabolites.

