#### Change in scores of TCM symptoms and signs

The TCM syndromes scoring system used in the study follows the guidelines of clinical research on the treatment of coronary heart disease (chest pain) with new Chinese medicine [14], in which all symptom and sign scores are graded (Table 4). A total of nine kinds of symptoms include: chest pain, chest tightness, breathlessness, palpitations, mental fatigue, aversion to cold, and cold limbs, lumbar and knee soreness, spontaneous sweating, and insomnia. The score is 0 points for asymptomatic, 1 point for mild, 2 points for moderate and 3 points for severe. The total score ranges from 0 to 27. The lower the score, the milder the symptoms.

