#### Data management and statistical analysis

The Drug Clinical Research Center of Guangzhou University of TCM will be responsible for the data statistical analysis. Two independent data administrators are in charge of reading the CRFs and recording data on the EpiData 3.1 software. Clinical research assistants (CRA) and investigators will re-check and review the accuracy and consistency of the data. After entering and reviewing, the database will be locked and the statistical analysis will be performed only with the permission of the sponsor, the principal investigator and the investigators.

The full analysis set (FAS) is the primary analysis set, in which patients should be dosed with *Guhong* injection or placebo for 10 days with clinical observations recorded in the study. All subjects without any major protocol deviations will be included in the per-protocol set (PPS). Efficacy assessment will be performed through FAS and PPS. Safety evaluation will be conducted for those who have been treated at least once, which is defined as the safety set (SS).

All continuous data and normal distribution data are represented by mean ± standard deviation, with median and range for non-normal data. Classified data are expressed in frequency counts and percentages. Baseline balance between groups will be determined by a chi-square test or analysis of covariance (ANOVA). All the indicators of anginal attack frequency, inflammation, endothelial function and myocardial metabolites will be estimated and compared using the log-rank test. A Kaplan-Meier survival curve will be constructed, and the median time will be provided separately for each group with a two-sided 95% confidence interval. ANOVA and Bonferroni methods will be used to compare the TCM symptom and sign scores of the two groups. All collected data will be processed by professional statisticians using SAS 9.2 software; a two-sided *P* value of < 0.05 is considered statistically significant.

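### The TCM score analysis names ANOVA with no covariate and an undefined Bonferroni step; it should name ANCOVA on the enrolment score and say what Bonferroni covers

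*Protocol article*

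**What the plan says.** The method is stated in the protocol article under Data management and statistical analysis: "ANOVA and Bonferroni methods will be used to compare the TCM symptom and sign scores of the two groups". No covariate, time point or family of comparisons is given. Earlier in the same paragraph the article says "Baseline balance between groups will be determined by a chi-square test or analysis of covariance (ANOVA"), which attaches the abbreviation for analysis of variance to the name of a different method.

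Under Interventions, the assessments on the day of enrolment and at the end of treatment include this one: "the quantitative table of TCM syndrome will be scored". The score is also followed after treatment: "patients will be followed up for 8 weeks after the end of treatment, including any improvement in angina pectoris and the TCM syndrome quantitative score". There is therefore one value before treatment and at least two after it.

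The outcome itself is worded as a change: "Secondary outcomes include changes in TCM symptoms and signs scores (Table 4"), and the section that defines it is titled in the same way. The scale adds nine symptoms, each graded 0 to 3: "The total score ranges from 0 to 27".

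**The concern.** Three things in these sentences do not fit together.

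- **Model.** A two-group ANOVA with no covariate leaves the enrolment score out of the model, although it is already collected and is usually the strongest predictor of the later score. The mislabelled abbreviation leaves open whether a covariate was intended.
- **Dependent variable.** The outcome section speaks of changes and the analysis section of scores. The article does not say which one enters the model.
- **Bonferroni.** Two arms give one contrast at each time point, so a correction needs a stated family of comparisons. None is given.

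At stake are the precision of one secondary comparison and the risk that model, time point and correction are settled after the results are known.

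**Working it through.** **The plan's own figure.** The article gives no SD, effect or power for the TCM score. Its only sample-size figure is 111 per group for the primary effective rate, at two-sided α = 0.05 and β = 0.2. With unpooled variance:

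[0.9394 × 0.0606 + 0.8182 × 0.1818] × (1.960 + 0.842)² / (0.9394 − 0.8182)² = 109.9, so 110 per group.

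The pooled form gives 113. The stated 111 is reproduced closely enough. It does not bear on the TCM score and serves below only as a realistic number per arm.

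**Inputs.** The enrolment score X and the later score Y come from the Interventions section. The correlation r between them is not in the document; I assume 0.3, 0.5 and 0.7. I also assume the same SD at both times, set to 1, and the same r in both arms.

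**Formula.** All three candidate analyses compare the arms on Y − bX. Its variance is 1 + b² − 2br.

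- ANOVA of the later score sets b = 0: variance 1.
- ANOVA of the change sets b = 1: variance 2(1 − r).
- ANCOVA estimates b, which here equals r: variance 1 − r². This is the minimum over b, so apart from the one degree of freedom spent on b it cannot be less precise than the other two.

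The ratio of ANCOVA to later-score ANOVA is 1 − r². The ratio of ANCOVA to change-score ANOVA is (1 − r²) / [2(1 − r)] = (1 + r)/2.

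| r | Later score | Change | ANCOVA | Saving against change | Saving against later score |
|---|---|---|---|---|---|
| 0.3 | 1.00 | 1.40 | 0.91 | 35% | 9% |
| 0.5 | 1.00 | 1.00 | 0.75 | 25% | 25% |
| 0.7 | 1.00 | 0.60 | 0.51 | 15% | 49% |

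**In terms of power.** With 111 per arm, later-score ANOVA has 80% power for a difference of (1.960 + 0.842) × √(2/111) = 0.376 SD. For that same difference:

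| r | Later score | Change | ANCOVA |
|---|---|---|---|
| 0.3 | 80.0% | 65.8% | 83.6% |
| 0.5 | 80.0% | 80.0% | 89.9% |
| 0.7 | 80.0% | 95.1% | 97.5% |

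Measured against later-score ANOVA, ANCOVA with 111 per arm is worth 111/0.91 = 122, 111/0.75 = 148 or 111/0.51 = 218 per arm.

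**Bonferroni.** If it is meant to cover two time points, each is tested at 0.05/2 = 0.025. The 80% power above then becomes about 71% per time point. If it is meant for a single two-group contrast, it changes nothing. The article does not say which applies.

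**The case against.** The strongest reply is that the article does not establish that the enrolment score goes unused. It expands the abbreviation ANOVA only once, and there as analysis of covariance. If the TCM sentence carries that meaning, nothing is lost. The outcome is also worded as a change, and a change already subtracts the enrolment value. Both points stand. A reader might infer that the plan discards the baseline and forfeits up to 49% of the variance, but that figure belongs to ANOVA of the later score, which the article never names as the outcome. Against the change, the saving runs from 35% down to 15% as r rises from 0.3 to 0.7. What the reply does not remove is that covariance analysis makes little sense for a balance test, so plain ANOVA remains the likelier meaning, and that ANCOVA is at least as precise under either choice of dependent variable.

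A reader might also infer that Bonferroni has no place in a two-arm trial. The score is followed beyond the end of treatment, so more than one comparison exists; the defect is only that the family is not stated. Nor does the article say that the TCM score is among the variables tested for baseline balance, so no claim rests on that.

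Finally, covariates for a secondary outcome often sit in a statistical analysis plan, and none is shown here. That is a fair limit. The point still stands because the article does name a method, and names it ambiguously.

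**Conclusion.** The point holds as a request to correct and sharpen a stated method. The label in the balance sentence is wrong, the model for the TCM score is ambiguous with plain ANOVA the likelier reading, and ANCOVA on the enrolment score is the better choice at no cost.

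The direction of the gain holds for any correlation strictly between 0 and 1. Its size rests on the assumed correlation and equal SDs, and on which analysis was intended: 35%, 25% or 15% of the variance against change-score ANOVA, 9%, 25% or 49% against later-score ANOVA, and none if ANCOVA was meant.

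The consequences are limited. Randomisation keeps the unadjusted comparison unbiased, and its standard error allows for chance imbalance at entry, so there is no validity problem. This is a secondary outcome; the primary effective rate and the total of 260 do not depend on it.

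**What to change.** Replace the TCM sentence with wording such as:

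> *The TCM score at the end of treatment and at 8 weeks will each be compared between groups by analysis of covariance with the enrolment score as covariate. The adjusted mean difference and its 95% confidence interval will be reported.*

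Then add that Bonferroni applies across these two time points, or remove it. If the study schedule (Table 2, not legible in the copy I had) lists a further follow-up score, include it in the family or say that it is descriptive. In the balance sentence, correct the pairing of analysis of covariance with ANOVA.

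Centre may be added as a further covariate, but this is optional: the envelopes are mixed and then sent out, with no stratification by centre described.

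The cost is a few lines of text, with no new data and no extra patients. Make the change before unblinding and date it. If a separate analysis plan already specifies ANCOVA, the two documents only need to be brought into agreement.

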#### Quality control and monitoring

All CRFs are designed in strict accordance with relevant requirements of GCP, which will be filled out by trained researchers to ensure consistency and reduce bias. If there is any ambiguity in the completion process, the results will be determined by the team members of the whole center after discussion. Each trial center has a project leader to control the quality, and all survey researchers are trained to be qualified and familiar with the process. In the process of clinical research, measures should be taken to ensure patient compliance according to the possible causes of loss to follow-up, and designated, special cardiologists will visit each center regularly to check the original documents and CRFs, and supervise the study to ensure that it complies with the protocol. Any shortcomings or problems found by the inspectors should be improved.

#### Interim analyses and stopping guidelines

When the trial is nearly halfway through, an interim analysis of the collected data will be performed. Only the sponsor and the principal investigator will have access to these interim results and decide whether or not to make the final decision to terminate the trial. The guidelines for stopping the trial are listed as follows: (1) The efficacy and safety of the studied drug have been confirmed; (2) The expected inter-group effect difference cannot be achieved and (3) There was an intolerable adverse drug reaction.

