### Randomization and blinding

A total of 260 participants will be randomly assigned to the *Guhong* group and the control group in a ratio of 1:1 by the method of using 260 opaque envelopes. Each envelope will be stuffed with a piece of paper. There are 260 pieces of papers in total, half of which have the words: “20 ml *Guhong* injection plus 250 ml 0.9% sodium chloride, ivd, qd” written on them and the other half have the words “270 ml 0.9% sodium chloride, ivd, qd” written on them. After all the opaque envelopes have been stuffed and sealed, they will be mixed evenly and distributed to each trial center.

When a sub-center accepts an eligible participant, the investigators will write the baseline information (including the subject’s hospital ID number, name, age and gender) on the cover of the envelope. Both investigators and participants will be blinded. Only drug administrators and dispensing nurses are responsible for opening the envelope to know the group allocation and perform the interventions according to the written instructions on the paper, but they won’t be involved in recruitment, recommendations, data collection and data analysis. Both the *Guhong* injection and placebo are administered using a photophobic infusion set to avoid the subjects being aware of the group information. All investigators, outcome assessors and data analysts will be blinded to collect and summarize the data which is only based on a subject’s baseline information until the completion of the visit and analysis.

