### Unblinding after the study

When all trials are completed and all data have been locked, the unblinding process will be conducted in the presence of the researchers.

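### The halfway interim allows an efficacy stop with no allowance in the stated 0.05 level, and gives the sponsor and principal investigator between-group results that the blinding sections rule out until data lock

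*Protocol article*

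**What the plan says.** **The look and its stopping grounds.** The section Interim analyses and stopping guidelines plans one analysis when the trial is close to its midpoint. It gives three grounds for stopping. The first is "1) The efficacy and safety of the studied drug have been confirmed". The second is that the hoped-for difference between the groups is out of reach. The third is an intolerable adverse drug reaction. None carries a number.

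**Who sees the results.** The same section states: "Only the sponsor and the principal investigator will have access to these interim results and decide whether or not to make the final decision". The decision meant is whether the trial ends early.

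**Blinding.** Randomization and blinding states: "All investigators, outcome assessors and data analysts will be blinded", and this lasts until visits and analysis are finished. Unblinding after the study states: "When all trials are completed and all data have been locked, the unblinding process will be conducted".

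**Significance level.** Sample size states: "the sample size was calculated based on the parameter *α* = 0.05 (bilateral test) and *β* = 0.2". Data management and statistical analysis states: "a two-sided *P* value of < 0.05 is considered statistically significant". Neither section mentions the interim look.

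**The concern.** Two stated rules collide with the interim section, and each matters by itself.

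*Access.* The first two stopping grounds cannot be judged without comparing the arms. The principal investigator is an investigator, so being shown that comparison mid-trial does not fit a rule that all investigators stay blinded until the analysis is done. Recruitment continues after the look. The primary outcome (Table 3) is graded partly on judgement, for instance whether attacks have improved markedly or whether the ECG is close to normal. Knowledge of the trend could affect enrolment, grading or the decision to go on.

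*Error control.* A trial that may claim efficacy at either of two analyses, each at 0.05, is not a 5% test. With no interim threshold stated, the two parties who hold the results could settle what counts as confirmed after seeing them.

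**Working it through.** **1. The plan's own figure.** Inputs from Sample size: effective rates 0.9394 and 0.8182, two-sided α = 0.05, power 80%, 1:1 allocation. The formula is printed without its squares; with them restored,

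n per arm = [0.9394 × 0.0606 + 0.8182 × 0.1818] × (1.960 + 0.842)² / (0.1212)² = 0.2057 × 7.849 / 0.01469 = 109.9.

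This gives 110 against the stated 111 (the pooled-variance version gives 113). Allowing for 15% attrition, 111 / 0.85 = 130.6 against the stated 130. The stated size is therefore reproduced, within rounding, by a single-look test at the full 0.05.

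**2. Two looks, both at 0.05.** Under no effect, the interim and final statistics (Z1, Z2) are bivariate normal with correlation √t, where t is the information fraction. Overall type I error = P(|Z1| > 1.96 or |Z2| > 1.96):

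| t | Type I error |
|---|---|
| 0.50 | 8.3% |
| 0.45 | 8.5% |
| 0.40 | 8.6% |

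A simulation with a binary outcome (65 then 130 per arm, 2,000,000 runs) gives 8.2%. Counting only false claims in favour of *Guhong*, the rate at t = 0.50 is 4.2% instead of 2.5%.

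**3. Sensitivity to the unstated interim rule.** Final test at 0.05, t = 0.50:

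| Interim threshold | Type I error |
|---|---|
| p < 0.05 | 8.3% |
| p < 0.0294 | 6.7% |
| p < 0.01 | 5.5% |
| p < 0.0052 | 5.2% |
| p < 0.001 | 5.02% |

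If both looks use 0.05 but the futility ground is binding, simulation gives 6.2% to 6.7% (stopping when Z1 is below 1.0 or below 0, respectively).

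**4. Boundaries that hold 5%.** At t = 0.50 the classical O'Brien-Fleming limits are |Z1| > 2.797 (p < 0.0052) and |Z2| > 1.977 (p < 0.0480). At the effect that gives a single-look test 80.0% power, they give 79.7%. The sample-size inflation is 1.008: 109.9 × 1.008 = 110.8, so 111 per arm still suffices. Pocock limits (p < 0.0294 at both looks) would need 1.110 × 109.9 = 122.0, so 123 per arm.

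The Lan-DeMets spending version differs slightly. At t = 0.50 it spends 4[1 − Φ(2.241/√0.50)] = 0.0031 at the interim, and solving for an overall 5% leaves about 0.0490 at the end.

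**5. What half means.** The plan counts on 2 × 111 = 222 evaluable patients, so half the information is about 111 patients with the outcome. A look at 130 evaluable patients (half of 260) would be at 130 / 222 = 59%.

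**6. Access, side by side.** The interim section shows the results to the sponsor and the principal investigator. The blinding section covers all investigators until the analysis is complete. The end-of-study section puts unblinding after completion and data lock. Two of the three stopping grounds need a between-group comparison. No reading satisfies all of these statements.

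**The case against.** **The boundary may sit in an unseen SAP.** Only a condensed article is available, and boundaries are commonly left to the analysis plan, so a missing boundary alone is no finding. That stands. The article, however, itself fixes an efficacy stop, an unqualified 0.05 and the people who see the results. An adjusted final level in an SAP would contradict the stated 0.05, and no boundary would resolve the access conflict.

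**A type I error of about 8% is not established.** A reader might infer that the trial runs at 8%. The interim section names no test or threshold, and the general 0.05 is not tied to the interim. The 8.3% to 8.6% is the upper end of a range that starts at about 5.0%.

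**Broken blinding is not established either.** A reader might infer that the double blind is lost. The interim section never uses the word unblinded; a between-group comparison is implied by its stopping grounds. Nothing says that individual allocations are disclosed or that site assessors learn anything, and access is limited to two parties. Groups could be shown under codes, although a judgement that efficacy is confirmed would tend to reveal the direction. What stands is a conflict at group level for the sponsor and the principal investigator.

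**Conclusion.** The point holds as a contradiction between stated rules. The interim section requires the sponsor and the principal investigator to judge a between-group result mid-trial, while the blinding sections keep investigators blinded until analysis and data lock. The efficacy stop also sits beside a single unadjusted two-sided 0.05.

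The size of the error inflation depends on a rule that the article does not state: from about 5.0% with a strict interim threshold to 8.3–8.6% if 0.05 is used at both analyses. These figures assume one look at 40% to 50% information, a normal approximation and, unless noted, non-binding futility. The possible effect on enrolment or grading cannot be quantified from the document.

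**What to change.** Make the change before the interim is run; a boundary chosen afterwards is not prespecified. Trial status reports enrolment as continuing but does not say whether the look has taken place.

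- **Option A:** restrict the interim to safety and drop the efficacy look. The final test then keeps 0.05.
- **Option B:** keep the efficacy look on the primary outcome and prespecify an O'Brien-Fleming-type Lan-DeMets spending boundary, computed at the actual information fraction, with non-binding futility at a stated threshold. For a look at exactly 50% (about 111 evaluable patients in total), the classical limits are p < 0.0052 at the interim and p < 0.0480 at the end.
- **Under either option:** amend the interim section so that the principal investigator and the sponsor's trial team receive only a continue-or-stop recommendation, and no between-group results, while the trial continues. A statistician outside the trial team can prepare it.
- **Reconcile** the interim section with Randomization and blinding, Unblinding after the study, and the 0.05 statement in Data management and statistical analysis.

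Cost: an amendment to the protocol and SAP, plus the outside statistician's time. Option B also lowers the final threshold to about 0.048 and costs about 0.3 points of power (80.0% to 79.7%), with no need to exceed 111 evaluable patients per arm.
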